### Study subjects

#### Inclusion and exclusion criteria

In this ongoing case-control study, already registered in ClinicalTrials.gov (Identifier NCT03885648), women’s age will range 25–70 years. Cases will be defined as women diagnosed and surgically intervened of incident breast cancer, stages I and II. Controls will be women surgically intervened of breast augmentation or reduction. Women with antecedents of cancer or advanced tumor stage (metastasis), or who have received antibiotic treatment within a period of 3 months prior to recruitment, or any neoadjuvant therapy, will be excluded of the study. Women with oncological, gynecological or endocrine antecedents and those who have received antibiotic treatment within a period of 3 months prior to recruitment will be also excluded. Controls will be matched to cases by age (± 2 years), category of body mass index and hospital of recruitment.

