#### Sample size

Sample size has been calculated taking into consideration the incidence of breast cancer in Spain, the female population of Andalusia and the formula described by Aguilar-Barojas (2005) [18]. Because of that, the number of breast cancer cases will include at least 100 women, matched with 100 control women subjected to breast reduction or augmentation. Three hospital centers will participate in the recruitment: The Unit of Mammary Pathology, General Surgery Service, University Hospital of Jaén, Spain; the Unit of Mammary Pathology, General Surgery Service, University Hospital Campus de la Salud, Granada, Spain; and Ana Moreno Clinic (Granada, Spain).

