### Quantitation of the exposure to EDCs in urine samples

Analysis of non-persistent EDCs will be carried out by dispersive liquid–liquid microextraction (DLLME) and ultra-high performance liquid chromatography with tandem mass spectrometry detection (UHPLC-MS/MS) as previously described with minor modifications [28, 29]. Briefly, urine samples will be thawed completely at room temperature, centrifuge at 2600 x g for 10 min to sediment particulate matter and 0.75 mL will be taken to carry out the analysis. In order to determine total EDCs amount (free plus conjugated) in urine, each sample will be spiked with 50 μL of enzyme solution (β-glucuronidase/sulfatase) and incubated at 37 °C for 24 h. The treated urine will be placed in a 15 mL screw-cap glass tube and spiked with 30 μL of the surrogate standard solution (1.25 mg/L of BPA-d_16_). Urine will be diluted to 10.0 mL with 5% NaCl aqueous solution (w/v) and the pH will be adjusted to 2.0. Next, 0.75 mL of acetone and 0.75 mL of trichloromethane will be mixed and injected rapidly into the aqueous sample with a syringe. After manual shaking, centrifugation and evaporation of the extract, the residue will be dissolved with 100 μL of a mixture consisting of water (0.1% ammonia)/acetonitrile (0.1% ammonia), 70:30 (v/v), and finally 10 μL will be injected in the LC system. Urinary creatinine concentration (mg/dL) will be determined using an automated colorimetric determination, in the same urine samples in which environmental chemical will be assessed. Because of the relatively constant excretion rate of creatinine into the urine (which makes urinary creatinine concentration inversely proportional to urine flow rate), creatinine adjustment is widely used to normalize analyte concentrations in spot samples for environmental exposure monitoring [30].

Bisphenols [bisphenol A (BPA), bisphenol S (BPS) and bisphenol F (BPF)], parabens [(metylparaben (MeP), ethylparaben (EtP) propylparaben (PrP) and butylparaben (BuP)], benzophenones [(UV filters: benzophenone-1 (BP-1), benzophenone-3 (BP-3) and 4-hidroxybenzophenone (4-OH-BP)] will be determined. Final concentrations will be adjusted for urinary creatinine levels (mg/dl), to account for both urine dilution and body composition, as previously reported [31, 32].

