Random forest (RF) is a supervised classification technique based on an ensemble of decision trees [35] with several advantages. It makes no parametric assumptions, and variable selection is not needed. It does not overfit, and it is invariant to transformation. In RF analysis, it is not necessary to cross-validate or do a separate test set to obtain an unbiased estimate of the test set error. A “variable importance” measure will be computed to determine which variables (metabolites) make the largest contribution to the classification. The mean decrease in accuracy (MDA) will be used as this metric and will be determined by randomly permuting a variable, running the observed values through the trees, and then reassessing the prediction accuracy. If a variable were not significant, then this procedure will have little change in the accuracy of the class prediction (permuting random noise will give random noise). By contrast, if a variable is relevant for the classification, the prediction accuracy will drop after such a permutation, which will be recorded as the MDA. Thus, the RF analysis provides an “importance” rank ordering for biochemicals [35].

Participants will be grouped into tertiles of urinary EDC levels based on their distributions among the controls. Odds ratios and 95% confidence intervals (CIs) for breast cancer comparing the second and third tertiles with the first tertile will be estimated using logistic regression models. Further, associations of participant characteristics with urinary EDC levels, estrogens and estrogen metabolites and fecal microbiome measures will be evaluated by using general linear models and testing either for differences across categories or for trends across categories. Linear regression models will also be used to evaluate associations of each steroid measure with measures of the diversity of the fecal microbiome, abundance and with taxonomic groups at phylum and family levels, adjusting by covariates.

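### The EDC-breast cancer association is estimated only by tertile contrasts; adding an odds ratio per doubling of concentration would gain power if the relation is roughly log-linear

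*Protocol article*

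**What the plan says.** The Statistical analysis section of the protocol article sets the exposure coding: "Participants will be grouped into tertiles of urinary EDC levels based on their distributions among the controls". It then sets the contrasts: "Odds ratios and 95% confidence intervals (CIs) for breast cancer comparing the second and third tertiles with the first tertile will be estimated", by logistic regression. No other EDC-breast cancer analysis is stated.

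The sentence that follows mentions "testing either for differences across categories or for trends across categories", but it concerns how participant characteristics relate to EDC levels, estrogens and fecal microbiome measures. The linear regressions after that relate steroid measures to the fecal microbiome. Neither covers EDC level against case status.

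The section on quantitation of EDCs in urine lists 3 bisphenols, 4 parabens and 3 benzophenones, 10 compounds in all, and says: "Final concentrations will be adjusted for urinary creatinine levels (mg/dl), to account for both urine dilution and body composition". A continuous exposure value is therefore planned for every woman and every compound.

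On size, the Sample size section says: "the number of breast cancer cases will include at least 100 women, matched with 100 control women".

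**The concern.** Grouping a measured concentration into thirds discards the differences within each third. Each of the two contrasts also uses only about two thirds of the women. If risk rises steadily with log concentration, both features cost power.

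The link between contaminant exposure and breast cancer risk is one of the study's stated aims, and the sample is modest. The third v first log odds ratio has a standard error of about 0.36, so its 95% confidence interval runs about a factor of 2 either way. A real monotone association of moderate size could be missed when data already collected would have shown it.

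**Working it through.** **The plan's own figure.** The article gives 100 cases and 100 controls, based on breast cancer incidence, the female population of Andalusia and a cited formula. It prints no incidence value, precision, effect size, alpha or power, so the figure cannot be reproduced. There is no stated power for the EDC analysis to compare with.

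**Inputs.** From the article: 100 v 100, control-based tertiles, and two-sided 0.05 (inferred from the 95% intervals). Assumed: the effect size (odds ratio 1.3 to 2.0 per SD of log concentration), the dose-response shape, normal log exposure, and an unmatched logistic model. Power per SD and per doubling is the same, because one is a rescaling of the other.

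**Hand check at OR 1.5 per SD, log-linear.** Let log exposure be N(0,1) in controls and N(ln 1.5, 1) in cases, with ln 1.5 = 0.4055. The control tertile cuts are ±0.4307.

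- Cases in the top tertile: 1 − Φ(0.4307 − 0.4055) = 0.490. Cases in the bottom tertile: Φ(−0.4307 − 0.4055) = 0.202.
- Implied OR, third v first: 0.490/0.202 = 2.43 (unrounded inputs); its log is 0.888.
- SE = √(1/33.3 + 1/33.3 + 1/49.0 + 1/20.2) = √0.130 = 0.36. Since exp(1.96 × 0.36) = 2.03, the interval is about a factor of 2 each way.
- Tertile z = 0.888/0.3606 = 2.46. Power = Φ(2.46 − 1.96) = 69%.
- Continuous z = 0.4055/√(2/100) = 2.87. Power = Φ(2.87 − 1.96) = 82%.
- Information ratio = (2.867/2.464)² = 1.35.

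**Simulation, log-linear effect (4,000 replicates per row; power in %).** T1, T2 and T3 are the tertiles.

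| OR per SD | Implied OR, T3 v T1 | Continuous | T3 v T1 | Loss (points) | 2-df tertile test | Ordinal tertile trend |
|---|---|---|---|---|---|---|
| 1.0 | 1.00 | 5.1 | 4.8 | – | 5.2 | 5.0 |
| 1.3 | 1.77 | 44.3 | 33.5 | 10.8 | 28.0 | 34.0 |
| 1.4 | 2.09 | 64.1 | 50.8 | 13.3 | 43.0 | 51.1 |
| 1.5 | 2.43 | 79.1 | 66.6 | 12.5 | 57.5 | 67.2 |
| 1.6 | 2.80 | 90.6 | 79.8 | 10.8 | 72.3 | 80.4 |
| 1.75 | 3.42 | 97.8 | 92.5 | 5.3 | 88.7 | 93.0 |
| 2.0 | 4.62 | 99.8 | 98.5 | 1.3 | 97.8 | 98.7 |

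Type I error is about 5% throughout. A trend test on tertile rank does not recover the loss; the measured concentration does.

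**Loss as sample size, OR 1.5.** The ratio is ((1.96 + z for continuous power)/(1.96 + z for tertile power))².

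- 79.1% v 66.6%: ((1.96 + 0.81)/(1.96 + 0.43))² = 1.34.
- Other simulation runs gave 80% v 67%, 82% v 68%, and 81% v 70 to 71%, with ratios of about 1.36, 1.40 and 1.29.

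The loss is therefore worth about 30 to 40% more women.

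**Other shapes, 100 v 100.** The step rows are from the 4,000-replicate run, the others from a separate run of 3,000.

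| Shape | Continuous | Tertile contrast |
|---|---|---|
| Step at T3, OR 2 | 46.6 | T3 v T1: 44.4 |
| Step at T3, OR 3 | 87.3 | T3 v T1: 87.2 |
| Plateau, T2 = T3, OR 2 | 35 | T3 v T1: 39 |
| T2 only, OR 2.5 | 4 | T2 v T1: 60 |

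**The case against.** The strongest reply is that nothing here is an error. Control-based tertile odds ratios are a conventional, valid case-control analysis and robust to skewed exposures. That stands. A reader might infer that the tertile estimates are biased or unsound; the documents and the calculations give no support for that.

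A second reply is that the log-linear simulation favours the continuous term by construction, because that is the setting in which the slope is the efficient test. This also stands. A reader might infer that tertiles lower power whatever the truth, or that a continuous term should replace them. Neither follows. The article states no dose-response shape, the gain vanishes for a step at the top tertile, and it reverses for a plateau. A linear term is almost blind to an effect confined to the middle tertile.

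A third reply is that an article condenses a fuller plan, which may contain a continuous or trend analysis. That may be so, and it cannot be inferred that the full plan lacks one. But the article is not silent here: it fixes the coding, the reference category and both contrasts. The point concerns that stated choice.

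Finally, values below detection and multiplicity across the 10 EDCs might seem to belong here. The article gives no detection rates, and neither question bears on the loss from grouping, so neither is part of this point.

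**Conclusion.** The point holds as a cheap improvement, not as a correction of a fault. As the article states it, the EDC-breast cancer association rests on two tertile contrasts although continuous concentrations will be available. If the relation is roughly log-linear, this costs about 10 to 13 power points at odds ratios of 1.3 to 1.5 per SD with 100 v 100. The cost shrinks to about 1 point at an odds ratio of 2.0.

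The size rests on assumed effect sizes, normal log exposure and an unmatched model. The article matches controls by age, body mass index category and hospital, which the calculations ignore. It also gives 100 cases as a minimum, so absolute power would be higher with more women.

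**What to change.** Keep the tertile odds ratios as planned, to show the shape. Beside them, prespecify a second fit of the same logistic model for each EDC, with log2 creatinine-adjusted concentration in place of the tertile indicators. Report it as an odds ratio per doubling with a 95% confidence interval, and name it as the test for a monotone dose-response.

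The cost is a sentence of analysis text and one extra fit per compound; no samples or assays are added. There are two downsides. The added estimate assumes log-linearity, so it must be read with the tertile odds ratios. It also adds one test per EDC, 10 in all. The article says that enrolment and data analysis are both continuing, so the addition should be dated and fixed before EDC levels are compared with case status.

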## Discussion

There are 7 studies registered in ClinicalTrials.gov dealing with breast cancer and microbiota, 2 already completed and 4 currently ongoing. Of the 2 completed studies, one investigated the antibiotic profilaxis in oncological surgery of the breast, and the other investigated the relationship between intestinal bacteria and breast cancer risk. As for the studies in progress, these are trials investigating various intervention strategies (probiotics, physical activity, diet), the effects of gut microbiome on the neoadjuvant chemotherapy-induced immunosurveillance in triple negative breast cancer, or the effects of chemotherapy on gut bacteria in newly diagnosed breast cancer. Our study is a case-control clinical trial that aims at ascertaining the connection relating i) the composition of both gut and breast microbiota, ii) the functionality of both gut and breast microbiota, and iii) the exposure to environmental contaminants with the risk of developing breast cancer. To the best of our knowledge, it is the first study undertaking the simultaneous analysis of the microbiota of the mammary tissue and the intestine, and also the first attempt to link the microbiome with the EDC load and the risk of this disease.

The microbiota is affected by either modifiable and unmodifiable factors such as genetics, stress, diet, physical activity, lactation, delivery mode, antibiotic treatment, smoking, age, and alcohol consumption, among others [36]. For this reason, in an attempt to control some of the modifiable factors, all participants will answer three questionnaires to record their sociodemographic data, adherence to the Mediterranean diet, and frequency of food consumption. For the same reason, we set stringent inclusion and exclusion criteria. Women participating in the study will be newly diagnosed cases of breast cancer. Therefore, women with antecedents of cancer or advanced tumor stage will not take part, nor those who have received antibiotic treatment 3 months prior to recruitment, or any neoadjuvant therapy. Likewise, regarding the controls, women with oncological, gynecological or endocrine antecedents and those who have received antibiotic treatment 3 months prior to recruitment will not be included.

The hypothesis of this study is that the risk of breast cancer could be associated with the composition and functionality of the mammary and/or intestinal microbiota. The hypothesis is supported by preliminary studies which suggest that the microbial pattern of women with breast cancer is different than that of healthy women, not only with regards to bacterial types and relative abundance, but also with their functionality (metabolic capacity, ability y to damage DNA, etc.) [27, 37–39]. Exogenous factors such as the exposure to EDCs might contribute to this altered pattern [40, 41]. These circumstances would attribute to the microbiota the possibility of acting as an additional environmental risk factor and a potential prognostic modulator of the disease.

Validation of the hypothesis could translate into new recommendations and guidelines of clinical practice to improve prevention and prognosis of breast cancer, alleviating the burden of this disease. Likewise, a better identification of those patients most likely to efficiently respond to treatment could derive, given the fact that efficacy of immunotherapy against cancer depends on patients’ intestinal microbiota [42, 43]. Finally, interventional clinical studies aimed at shifting the mammary/gut dysbiosis of women affected by breast cancer toward a composition similar to that of healthy women could be designed.

## Abbreviations

4-OH-BP: 4-hidroxybenzophenone
AUC: Area-under-the-curve
BFS: Bisphenol S
BP-1: Benzophenone-1
BP3: Benzophenone-3
BPA: Bisphenol A
BPF: Bisphenol F
BuP: Butylparaben
CIE-0-2: Classification of Oncological Diseases
DLLME: Dispersive liquid–liquid microextraction
EDCs: Endocrine disruptors
EI: Electron impact ionization
EtP: Ethylparaben
GC: Gas chromatography
GI: Gastrointestinal
LC: Liquid chromatography
MDA: Mean decrease in accuracy
MeP: Metylparaben
MS: Mass spectrometers
PCR: Polymerase chain reaction
PERMANOVA: A permutation ANOVA
P-H2AX: Phosphorylated histone 2AX
PrP: Propylpaaben
QC: Quality control
RF: Random forest
RI: Retention index
RSD: Relative standard deviation
TNM: Tumor (T), nodes (N), and metastases (M)
UHPLC-MS/MS: Ultra-high performance liquid chromatography with tandem mass spectrometry detection
UPLC: Ultra performance liquid chromatography
UV: Ultraviolet
